#### 2.2.3. Measures

In order to alleviate the discomfort that the bereaved may feel when filling in the questionnaires, the researchers will try to reduce the number of the items as much as possible. Table 1 shows all the measures that will be carried out at each time point.

##### Demographic and Loss-Related Information

Demographic information includes age, sex, education level, marital status and religious belief. Loss-related information includes the relationship with the deceased, time since the loss, and the cause of death.

##### Primary Outcomes

Prolonged Grief Questionnaire (PG-13) [8] and Inventory of Traumatic Grief (ITG) [36] will be used to measure the grief symptoms of the bereaved. Post-traumatic stress symptoms will be assessed by the 20-item PTSD Checklist for DSM-5 (PCL-5) [37]. Depression Anxiety and Stress Scale (DASS-21) [38] will be used to measure the depressive symptoms, anxiety symptoms, and stress status of the bereaved. Posttraumatic Growth Inventory (PTGI) [39] will be used to assess the perceived benefits from traumatic events.

##### Secondary Outcomes

The Scale for Suicidal Intention (SSI) [40] will be used to measure the severity of suicidal intentions. Maladaptive cognitions common in the bereaved will be measured by the Typical Beliefs Questionnaire (TBQ) [41]. The Grief-related Avoidance Questionnaire (GRAQ) [9] will be used to assess the avoidance behaviors of the bereaved. The Work and Social Adjustment Scale (WSAS) [42] will be used to assess the participants’ functioning in work, social adjustment, management, and family relationships.

### 2.3. Study 3: Grief Counseling for Bereaved Chinese during COVID-19

Based on the above grief therapy description, combined with the results of study two, the researchers will develop an online grief counseling plan that is more suitable for Chinese culture. The counseling is expected to include 8–10 sessions (one hour per session). The themes of each of the sessions are: (1) understanding and accepting grief reactions; (2) managing painful emotions; (3) learning to care for yourself; (4) increasing contact with others; (5) coping with difficult days; and (6) adapting to a new life.

#### 2.3.1. Sample

One-hundred-sixty bereaved Chinese will be recruited online. The inclusion criteria in study three are the same as study two.

#### 2.3.2. Procedure and Measures

The researchers aim to conduct a single-blinded randomized controlled trial (RCT) evaluating the effectiveness of grief counseling versus a waitlist control group in reducing prolonged grief symptoms, post-traumatic symptoms, depression levels, and suicidal intentions in bereaved Chinese individuals in relation to COVID-19.

After finishing the baseline questionnaires and signing the informed consent, 160 bereaved participants will be randomly assigned to the grief counseling group or the waitlist group.

The sample size is calculated based on the expected difference on the primary outcome variable (grief symptoms of the bereaved) between the different groups. According to previous RCTs on bereaved individuals [43], we expect a medium Cohen effect size of 0.5 in the intervention group. The sample size calculation is based on the conventional significance (α) and power (1−β) levels of 0.05 and 0.80, respectively, and an expected dropout percentage of 20%. The result shows that we will need almost 80 participants for each group, therefore, we have determined the total sample size to be 160 in this study.

The measures in study three are the same as study three. Assessments will be conducted at three time points: before randomization (baseline, T0), at post-counseling (T1), and three months after the post-counseling (T2).

Table 2 shows which measures will be assessed at each time point. And Figure 1 shows the research process.

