## Abstract

COVID-19 has caused nearly 4.3 million deaths all around the world. People who have experienced loss during this special period may find it difficult to adapt to life after loss, and may even suffer from prolonged grief disorder or other mental health problems. However, there is a huge gap of grief research in China, with almost no comprehensive grief intervention training system or very few professional grief consultants. Considering the large number of bereaved individuals who are suffering from grief and other mental health problems, it is significant to develop a suitable and effective intervention protocol immediately. This article illustrates a study protocol initiated by a Chinese university to investigate the mental health of bereaved individuals during the COVID-19 pandemic and train grief counselors to provide grief counseling to the bereaved, as well as to evaluate the effectiveness of the grief counseling. The method is as follows: (1) 300 psychological counselors will be recruited to attend the grief counseling training. Assessments will be conducted at three time points: baseline (T0), after the basic training (T1), and after the advanced training (T2); (2) 500 bereaved Chinese will be recruit to join the online survey and will be assessed at two time points with a six-month interval; and (3) a two-armed (grief counseling versus wait-list controls) RCT (random control trials) will be conducted with 160 bereaved individuals. Assessments will be conducted at three time points: before randomization (baseline, T0), at the post-counseling (T1), and three months after the post-counseling (T2). Primary outcomes will be assessed by the Prolonged Grief Questionnaire (PG-13), the 20-item PTSD Checklist for DSM-5 (PCL-5), the Depression Anxiety and Stress Scale (DASS-21), and the Posttraumatic Growth Inventory (PTGI). This research will help develop grief research and grief counseling in China, as well as provide professional mental health services for individuals who may suffer from grief-related disorders in the future.

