## 3. Statistics Analyses

IBM SPSS Version 25 (Armonk, New York, USA) will be used to analyze the data. Both completer analyses and intention-to-treat analyses (using the method of last observation carried forward) will be carried out. Descriptive characteristics of the sample will be calculated as obtained counts (*n*) and simple proportions (%), with missing items reported as missing.

For study one, the measurements at three different time points will be compared using the analyses of variance (ANOVA) for continuous variables and the chi-square test for categorical variables.

In addition, in study two, the researchers will employ linear regression analyses to examine the predictors of PG-13, DASS-21, PCL-5 and PTGI at each time point, while controlling for gender, age, education level, marital status, and religious beliefs. The cross-lagged model will be used to further clarify the direction of the relationship between the predictors and outcome variables. A *p*-value < 0.05 (2-tailed) will be taken to indicate statistical significance.

For study three, Chi-square tests and ANOVAs will be conducted on baseline scores to rule out significant differences between groups on demographic or loss-related or outcome variables before treatment. The treatment effects on the primary outcome variables will be examined with a 2 (groups) × 3 (time points) multivariate analysis of variance (MANOVA), with three time points (baseline, post-counseling, and three months follow-up) as the repeated measures. The outcomes of treatments will be further investigated separately with the analyses of covariance (ANCOVA), using baseline scores of the outcome variables as covariates.

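### Study 3's treatment test includes post-traumatic growth (PTGI), which is outside the trial's stated aim, so the primary test can be positive with no reduction in any targeted symptom

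*Protocol article*

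**What the plan says.** **Aim.** Section 2.3.2 describes a single-blinded trial of grief counseling against a waitlist, judged by its effectiveness "in reducing prolonged grief symptoms, post-traumatic symptoms, depression levels, and suicidal intentions in bereaved Chinese individuals". That names four constructs, all of them to be reduced.

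**Sizing.** The same section bases the sample size on a single primary variable, grief symptoms. It assumes d = 0.5, α = 0.05, power 0.80 and 20% dropout, and arrives at almost 80 per group, 160 in total.

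**Primary outcomes.** The Abstract, directly after describing the trial, gives four scales: "Primary outcomes will be assessed by the Prolonged Grief Questionnaire (PG-13), the 20-item PTSD Checklist for DSM-5 (PCL-5"), then "the Depression Anxiety and Stress Scale (DASS-21), and the Posttraumatic Growth Inventory (PTGI"). Section 2.2.3 has the same scales plus the ITG under Primary Outcomes. It says of growth: "Posttraumatic Growth Inventory (PTGI) [39] will be used to assess the perceived benefits from traumatic events". It says of the DASS-21 that it "will be used to measure the depressive symptoms, anxiety symptoms, and stress status of the bereaved". Under Secondary Outcomes it says: "The Scale for Suicidal Intention (SSI) [40] will be used to measure the severity of suicidal intentions".

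Section 2.2.3 belongs to Study 2. Section 2.3.2 refers Study 3's measures back to Study 3 itself, evidently a slip for Study 2, and Table 2 lists the same scales for the trial.

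**Test.** Section 3 states: "The treatment effects on the primary outcome variables will be examined with a 2 (groups) × 3 (time points) multivariate analysis of variance". Separate baseline-adjusted ANCOVAs follow, without naming the outcomes they cover.

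**The concern.** PTGI measures a gain, not a symptom, and growth is not among the four constructs by which Section 2.3.2 defines effectiveness. It nevertheless enters the analysis that examines treatment effects, on the same footing as grief and post-traumatic symptoms. A significant result from that analysis therefore need not mean that anything in the aim has improved.

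This is separate from error control. With the type I error held exactly, an effect on PTGI alone would be a true positive, but on a construct the trial did not set out to change. At stake is whether a positive primary analysis can be reported as effectiveness in the sense of Section 2.3.2. The article gives no rule that decides this.

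**Working it through.** **1. The plan's own figure.** Two-sided α = 0.05, power 0.80, d = 0.5. (Section 3 states two-tailed testing in the Study 2 paragraph; it is assumed here for Study 3.)
- Normal approximation: 63 per arm, and 63/(1 − 0.20) = 79.
- t-test: 63.8, rounded up to 64 per arm, and 64/0.80 = 80, total 160.

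The stated size is reproduced. With 64 evaluable per arm, power for grief symptoms is 0.80.

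**2. Aim against tested set.**

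| Construct | In the aim (2.3.2) | Scale | Status |
|---|---|---|---|
| Prolonged grief | yes, and sizing variable | PG-13 (ITG also in 2.2.3) | primary |
| Post-traumatic symptoms | yes | PCL-5 | primary |
| Depression | yes | within DASS-21 | primary |
| Suicidal intention | yes | SSI | secondary |
| Perceived growth | no | PTGI | primary |

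The sets overlap on the first three rows. The last row is the fault.

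**3. Pooled test when only PTGI moves.** Take n = 64 per arm, p standardised scales, one follow-up, and a between-arm difference vector δ that is zero except for d on PTGI. Hotelling's T² has noncentrality λ = (n/2) δ′R⁻¹δ, and F has p and 2n − p − 1 degrees of freedom. Here λ = (n/2) d²/(1 − R²), where R² is the squared multiple correlation of PTGI with the symptom scales. The article gives no correlations. Assumed: 0.4 to 0.7 among symptom scales, 0 to 0.2 between these and PTGI.

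Four scales, d = 0.5:
- PTGI uncorrelated with symptoms: λ = 32 × 0.25 = 8.0; F critical value 2.445 on 4 and 123 df; rejection probability 0.59.
- Correlation 0.2 with PTGI and 0.4 among symptoms: R² = 3 × 0.04/(1 + 2 × 0.4) = 0.067; λ = 8.0/0.933 = 8.57; probability 0.62.

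Over the same assumptions, four scales give 0.23 to 0.24 at d = 0.3 and 0.89 to 0.92 at d = 0.7.

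Five scales (ITG added), d = 0.5: λ = 8.0 on 5 and 122 df gives 0.54; with the 0.2 and 0.4 correlations, λ = 8.63 gives 0.58.

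**4. Closer to the 2 × 3 design.** A simulation tested the changes from baseline at both later time points jointly, with 1,500 runs per setting, correlations of 0.6 among symptoms, 0 with PTGI and 0.5 over time, and d on PTGI only.

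| Setting | Proportion significant |
|---|---|
| 4 scales, 64 per arm, d = 0 | 0.05 |
| 4 scales, 64 per arm, d = 0.3 | 0.21 |
| 4 scales, 64 per arm, d = 0.5 | 0.61 |
| 4 scales, 64 per arm, d = 0.8 | 0.97 |
| 4 scales, 80 per arm, d = 0.5 | 0.73 |
| 5 variables, 64 per arm, d = 0.5 | 0.56 |
| 6 variables, 64 per arm, d = 0.5 | 0.48 |

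Three other correlation sets, with four scales, 64 per arm and d = 0.5, gave 0.60, 0.60 and 0.85.

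**The case against.** **The scenario is constructed.** Growth moving with every symptom scale exactly still is an assumption; nothing in the article predicts it. That stands. The figures show what the test permits, not what is likely.

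**The MANOVA may not be pooled.** The wording could mean a repeated-measures analysis per scale. Then the pooled probabilities do not apply, but PTGI remains one of several primary results that could be called positive.

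**The ANCOVAs would reveal a PTGI-only effect.** They would, and the plan does not instruct anyone to read growth as symptom reduction. But it does not say which result supports the conclusion either.

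**Stronger readings a reader might infer.**
- *The aims and the tested outcomes are different sets.* They are not: grief, post-traumatic symptoms and, within DASS-21, depression are in both, and the sizing variable is in both.
- *Suicidal intention goes untested.* Serving an aim with a secondary outcome is not an error in itself. SSI is collected at all three time points, and the ANCOVA sentence is not limited to primary outcomes.
- *A depression effect will be diluted by anxiety and stress.* That happens only if a DASS-21 total is analysed. The article does not say so, and scoring is ordinarily left to the analysis plan.

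**Conclusion.** The concern holds for PTGI. The article defines effectiveness as symptom reduction and sizes the trial on grief, but runs its treatment test on a set of outcomes that includes perceived growth. Under the pooled reading, a PTGI-only effect of d = 0.5 gives a significant test with probability about 0.54 to 0.62 at 64 analysed per arm with four or five scales, and roughly 0.48 to 0.85 once other assumed correlations and a sixth variable are allowed. All of these depend on correlations the article does not supply. Under the per-scale reading no such figure applies, but the gap between test and conclusion remains. The design and sample size are sound on this point. The correction is one of wording, and should be made before the data are analysed.

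**What to change.** In Section 3, for Study 3:
1. State that the effectiveness conclusion rests on the baseline-adjusted ANCOVA of grief symptoms measured by PG-13. Grief is the outcome the trial is sized on, and PG-13 is the grief scale the Abstract lists as primary.
2. Take PTGI out of the treatment-effect MANOVA and report it as secondary. If the sponsor does regard growth as an aim, add it to the aim sentence in Section 2.3.2 and state that an effect on PTGI alone is not symptom reduction.
3. Report PCL-5, the DASS-21 depression subscale and SSI by the same ANCOVA as supporting outcomes, naming SSI explicitly.

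Making all four aim constructs separately decisive would be a poor substitute. Without a decision rule, four independent tests at 0.05 carry a family-wise error of 1 − 0.95⁴ = 0.185 (less if correlated), and this would depart from the single sizing variable.

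Cost: wording only. Table 2 already collects every scale at all three time points, and the total stays at 160. The small downside is that PTGI loses its primary label in Study 3; its role in Study 2 need not change.

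### The RCT is sized on one grief outcome, but four or five instruments are called primary and tested, with no stated deciding test

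*Protocol article*

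**What the plan says.** All references are to the protocol article.

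- **Sizing (2.3.2).** The calculation uses "the expected difference on the primary outcome variable (grief symptoms of the bereaved) between the different groups". It gives an effect size ("we expect a medium Cohen effect size of 0.5 in the intervention group") and "levels of 0.05 and 0.80, respectively, and an expected dropout percentage of 20" per cent, and arrives at about 80 per group. It names no instrument and no visit.
- **Abstract.** Directly after describing the RCT it states: "Primary outcomes will be assessed by the Prolonged Grief Questionnaire (PG-13), the 20-item PTSD Checklist for DSM-5 (PCL-5", and the list goes on to DASS-21 and PTGI. That makes four instruments, and ITG is not among them.
- **Primary Outcomes (under 2.2.3, Study 2).** Five instruments appear, because ITG is paired with PG-13: "Inventory of Traumatic Grief (ITG) [36] will be used to measure the grief symptoms of the bereaved". Section 2.3.2 carries a measures list over to the RCT through a sentence that refers to itself. Study 2 is evidently meant, since Table 2 schedules all five instruments at baseline, post-counseling (T1) and three months later (T2).
- **Analysis (3).** The primary outcomes, in the plural, enter a MANOVA of two groups by three time points. Then: "The outcomes of treatments will be further investigated separately with the analyses of covariance (ANCOVA"), with baseline scores as covariates. Completer and last-observation-carried-forward ITT versions are both planned. The text does not rank the instruments, visits, models or analysis sets, and does not make the ANCOVAs depend on the MANOVA.

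**The concern.** The sample size treats the trial as having one primary outcome, while the outcome lists and the analysis treat it as having several. Grief itself does not settle which test counts, because one list measures it with two scales.

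Two things are at stake. First, counseling could be called effective because any one of several tests reached 5%, and the chance of such a result with no true effect is well above 5%. Second, the stated 80% power belongs to a single two-group comparison of a single outcome. It does not carry over to a requirement on several outcomes, or to tests at a reduced alpha.

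**Working it through.** **1. Reproduce the stated sample size.** Inputs from 2.3.2: d = 0.5, alpha 0.05, power 0.80, dropout 20%. Section 3 gives sidedness in its Study 2 paragraph ("0.05 (2-tailed) will be taken to indicate statistical significance"), and I assume that it applies to the RCT.

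- Normal approximation: n = 2(1.960 + 0.842)² / 0.5² = 62.8, so 63 per arm; 63 / 0.80 = 78.75, so 79.
- Exact t-test: 63.77, so 64 per arm; 64 / 0.80 = 80.
- A one-sided test would give 50, or 63 after dropout, which does not match.

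The plan's figure is right, as one unadjusted two-group comparison of one outcome at two-sided 0.05.

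**2. Count the tests.** The article does not say how many ANCOVAs there will be, so I bracket the number:

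- four instruments at one visit: 4 tests
- four at T1 and T2: 8 tests
- five at T1 and T2: 10 tests

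**3. Chance of at least one false positive, no true effect, each test at 0.05, no gate.** If the tests were independent, 1 − 0.95^m gives 18.5% (m = 4), 33.7% (m = 8) and 40.1% (m = 10). The outcomes will be correlated, and the article gives no correlations. I therefore simulated correlated normal test statistics (400,000 replicates) with an assumed between-visit correlation of 0.6:

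| Instruments × visits | outcome corr. 0.5 | 0.7 | 0.8 |
|---|---|---|---|
| 4 × 1 | 15.6% | 13.0% | 11.4% |
| 4 × 2 | 26.1% | 21.8% | 19.4% |
| 5 × 2 | 30.1% | 24.6% | 21.3% |

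**4. The same, if a 5% omnibus test had to be passed first.** I used a joint chi-square test on the post-baseline differences as a stand-in for the MANOVA. With no effect on anything, the chance of a false claim falls to about 4% at outcome correlation 0.5 and about 3% at 0.8.

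**5. Gate in place, but only PG-13 truly responds.** Take d = 0.5 at both visits and 64 per arm, so the PG-13 statistic has mean 0.5 × √(64/2) = 2.83. The chance of passing the gate and also finding some other instrument significant is:

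- four instruments: about 20% (outcome correlation 0.5) and 18% (0.7)
- five instruments: about 24% (0.5) and 22% (0.7)

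The real PG-13 effect opens the gate, and the other tests are then unprotected.

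**6. Cost of keeping all of them primary.** With Bonferroni adjustment at d = 0.5, 80% power per test and 20% dropout, the t-test needs 114 per arm (4 tests), 132 (8) or 137 (10). At 64 evaluable per arm, power per test would instead be 62%, 52% or 49%.

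**The case against.** **The SAP may settle this.** Hierarchy, alpha allocation and the choice of main analysis set are commonly left to a SAP or full protocol, and neither is shown. That stands for the alpha rule and for completers versus ITT, and their absence alone would be no finding. It does not dispose of the point, because one primary outcome in 2.3.2, four in the abstract and five in the Primary Outcomes list is a disagreement within the published text.

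**The analysis may be an omnibus test with follow-up.** Section 3's wording allows this. Under that reading the 11-30% range does not apply when nothing differs. But no such condition is written, and step 5 shows what a gate would leave open.

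**The test count is inferred.** This stands. Section 3 does not say that ANCOVAs are run at both follow-ups, and the fifth instrument comes from the Study 2 list. Hence the bracket in step 2; every ungated case in it exceeds 5%.

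**The text leans towards PG-13.** This stands too. The abstract and Section 3's Study 2 outcome list name PG-13 and omit ITG. The choice between the two scales is less open than the Primary Outcomes list alone suggests.

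A reader might also infer two further faults that the document does not support:

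- *That the MANOVA is underpowered.* At 64 per arm, the group-by-time test on PG-13 has power 0.83 if d = 0.5 holds at both visits (correlation 0.5). It falls to 0.71 only if the effect is assumed to halve by T2, and returns to 0.81 for that same case at correlation 0.6. No passage states such a decline.
- *That suicidal intention has become a further primary outcome.* The aim sentence in 2.3.2 ("reducing prolonged grief symptoms, post-traumatic symptoms, depression levels, and suicidal intentions") says what the trial evaluates. An aim may include a secondary outcome.

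**Conclusion.** The point holds as an inconsistency over what is primary, with a consequence for error rates that depends on how Section 3 is read. The sample-size arithmetic is correct, but its 80% power covers one comparison of one outcome.

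Without a gate, the false-positive chance under no effect is about 11-16%, 19-26% or 21-30%, depending on the test count. With a MANOVA gate it is about 4% when nothing differs, but about 18-24% for a false claim on another outcome when only PG-13 responds. The ungated ranges assume outcome correlations of 0.5-0.8 and the gated 18-24% assumes 0.5-0.7; all take 0.6 between visits. None of these correlations comes from the document.

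It would go too far to say that the trial's error rate is 30% or more outright, since that needs the largest test count, the lower correlations and no gate together. It would also go too far to say that the sample size already points to baseline-adjusted PG-13 at T1: section 2.3.2 fixes no instrument, visit or covariate.

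**What to change.** Name one confirmatory test in 2.3.2 and Section 3: one instrument, one visit and one model, in all randomised participants, at two-sided 0.05.

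- **Instrument.** PG-13 is the natural choice, as the only grief scale in both primary lists.
- **Visit and model.** Post-counseling (T1), counseling minus waitlist, adjusted for baseline PG-13, is a reasonable choice that keeps 160 participants. The sponsor must make it, because the document does not.
- **Everything else.** Make ITG, PCL-5, DASS-21, PTGI and PG-13 at the other visit secondary, under a Holm adjustment or a fixed testing order. Label the MANOVA supportive.
- **Alignment.** Bring the abstract, the Primary Outcomes list and 2.3.2 into line, and correct the self-referring sentence about the RCT measures.

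The cost is wording only, and the sample size does not change. The downside is that the other instruments lose the label of primary. Keeping all of them primary under Bonferroni would take 228 participants (4 tests) to 274 (10 tests).
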